#### **Variables to be Measured**

Please see uploaded instruments in appendix.

Under the leadership of [name] (Project Statistical Consultant), the team will use a variety of statistical methods to address the primary aims. Preliminary and descriptive analyses will inform subsequent analyses. Graphical representations will help identify aberrations, outliers, and missing data. Skewed data will be transformed or non-parametric approaches used when appropriate. We will start with basic methods, such as the comparison of rates of treatment initiation using chi-squared tests, and then proceed to analyses that may include adjustment for possible confounders and/or effect modifiers. Although we do not anticipate confounding due to an imbalance in covariates because of the RCT design, we will nevertheless test for differences in covariate distribution between study arms. If such imbalance is detected for specific covariates, we will introduce those covariates in the regression models. An indicator variable for site (Cincinnati, Columbus) will be included in all such models. We will use logistic regression models for the binary outcomes associated with initiation in mental health services. For analyses involving the number of follow-up visits, we assume a Poisson distribution. Accordingly, we will use Poisson regression models to assess differences in the number of follow-up visits between groups adjusted for potential confounders, if necessary. In all analyses, we will test for effect modification (interaction) by patient characteristics and study site. In the unlikely event that there is an interaction between study arm and study site, we will report site-specific results. We will use regression diagnostics to check our models for co-linearity and influential observations, using residual plots and associated quantitative methods.

Our primary analyses will compare STAT-ED and EUC using ITT analyses. Analysis by ITT requires that outcomes will be analyzed by randomization without regard to subject adherence to the study protocol. We will perform analyses to characterize participants who leave the study early relative to others.

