Hypothesis 1: STAT-ED will be superior to EUC in improving treatment initiation and overall treatment attendance. We will compare the rate of mental health treatment initiation in the STATED and EUC groups using the standard chi-square test of proportions. We plan to calculate effect sizes and confidence intervals in addition to simple tests of significance. As mentioned earlier, logistic regression models for adjustment will be used in the event of imbalance in any important covariates. We will compute the number needed to treat to benefit (NNTB) as an additional measure of the clinical significance of the impact of the STAT-ED intervention on treatment initiation rates relative to EUC. The analysis of overall number of treatment sessions attended by participants in each arm will use a likelihood ratio test based on the Poisson distribution. Similar to the analysis of treatment initiation, Poisson regression models will be used if covariate adjustment is necessary or for assessment of effect modification.

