### **Sample Size Justification**

Power analyses. All power calculations are for 2-sided tests,  $\alpha=0.05$ , and require power of 80%.

The primary outcome of mental health treatment initiation used in the sample size calculation is the proportion of participants who have attended at least one mental health visit in the 2 months after the ED visit, as assessed by the independent evaluator and verified with the mental health provider. Using a  $\chi^2$  test of proportion with continuity correction, power estimates for detecting differences in rate of treatment initiation during follow-up in the intervention and control group were computed using an expected rate of treatment initiation of 50% in the EUC arm. Under this assumption, the study will require 66 patients per treatment group to detect an intervention effect of 50% improvement in mental health treatment initiation (Table 4). We increased the number of participants to 80 per group to account for possible attrition and the chance of a lower rate of treatment initiation in the EUC group. With regard to the number of overall outpatient treatment sessions attended during follow-up, with 80 participants in each group, we are able to detect a difference in mean number of visits of between 1.7 and 2.2 (98). These calculations were based on an expected standard deviation  $\approx$  4.0-4.5 visits obtained from data reported by Spirito (34), Rotheram-Borus (33), and Asarnow (35).

On the basis of prior work, we anticipate retaining over 85% of participants for repeated assessment. For the primary aim, we will use an intent-to-treat analysis (ITT), and hence retain all 160 subjects. We will monitor the reasons for withdrawal, and use sensitivity analysis with missing data methods to assess the effects of withdrawal.

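### The number of sessions attended is tested with a Poisson likelihood ratio test, but the planning SD of 4.0-4.5 visits and 50% initiation rule out a Poisson distribution, so the type I error would be several times the nominal 5%

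*Protocol*

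**What the plan says.** Hypothesis 1 of the primary aim (Protocol, Purpose) has two parts: starting treatment, and attending more sessions in the two months after the ED visit.

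For the second part, Variables to be Measured states: "For analyses involving the number of follow-up visits, we assume a Poisson distribution". The Hypothesis 1 paragraph in the same section then fixes the test: the comparison of sessions "will use a likelihood ratio test based on the Poisson distribution". It adds that "Poisson regression models will be used if covariate adjustment is necessary or for assessment of effect modification". No dispersion parameter, robust variance or alternative count model is named.

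Sample Size Justification plans the same outcome from an SD: "These calculations were based on an expected standard deviation" of about "4.0-4.5 visits obtained from data reported by" three cited studies. With 80 per group it gives a detectable difference of 1.7 to 2.2 visits. The same section powers treatment initiation "using an expected rate of treatment initiation of 50% in the EUC arm".

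**The concern.** The two sections describe the same count in ways that cannot both be true. A Poisson test takes its standard error from the mean alone. If the true variance is larger than the mean by a factor phi, that standard error is too small by the square root of phi and the test rejects too often. An SD of 4.0-4.5 visits with half the comparison arm at zero points to a large phi.

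Sessions attended belong to the primary aim. If STAT-ED had no effect on attendance, the stated test could still report a significant difference much more often than 5% of the time, with an interval that overstates the precision.

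**Working it through.** **Inputs.** SD 4.0-4.5 visits (variance 16 to 20.25), 80 per group, 50% initiation in EUC, two-sided alpha 0.05 and 80% power, all from Sample Size Justification ("All power calculations are for 2-sided tests"). The mean number of visits is not given and is an assumption wherever it appears below.

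**1. The plan's own figure.** Detectable difference = (1.96 + 0.842) × SD × √(2/80).
- SD 4.0: 1.77 visits.
- SD 4.5: 1.99 visits.

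The stated range of 1.7 to 2.2 contains these values, although its end points do not reproduce exactly (2.2 matches SD 4.5 with 66 per group, at 2.195). Either way, the calculation rests on an SD and not on a Poisson variance.

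**2. What a Poisson distribution would require.** SD 4.0-4.5 needs a mean of 16 to 20.25 visits, which leaves practically no zeros. Zeros at 50% need exp(−mean) = 0.5, so a mean of ln 2 = 0.69 and an SD of 0.83. No single Poisson distribution meets both.

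**3. A bound that needs no assumed mean.** If a share p attends at all, variance ≥ mean² × (1 − p)/p, with equality when all attenders have the same number of visits. At p = 0.5 the mean cannot exceed the SD. So phi = variance/mean is at least 16/4.0 = 4.0 (SD 4.0) or 20.25/4.5 = 4.5 (SD 4.5).

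**4. Type I error.** The Poisson likelihood ratio statistic behaves like phi times a chi-square on 1 df, so the two-sided error is 2 × [1 − Φ(1.96/√phi)].
- phi 4.0: 32.7%.
- phi 4.5: 35.6%.

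This takes the SD as covering all randomised participants, as the power calculation uses it, and 50% initiation in both arms under the null.

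**5. By assumed mean** (same formula):

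| Mean visits | SD 4.0 | SD 4.5 |
|---|---|---|
| 2 | 48.8% | 53.8% |
| 2.5 | 43.8% | 49.1% |
| 3 | 39.6% | 45.1% |
| 4 | 32.7% | 38.4% |

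Simulations of 20,000 trials with 80 per arm agree within about one point, both with negative binomial counts and with 50% zeros plus a positive count for attenders. The errors are two-sided and, under the null, about half favour STAT-ED: half of 33-54% is about 16-27%.

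**6. If 75% initiated in both arms.** The mean could be as high as SD × √3 = 6.93 or 7.79. Phi is then at least 2.31 or 2.60, and the error at least 19.7% or 22.4%.

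**7. Interval width.** Intervals are too narrow by √phi: at least √4.0 = 2.0 to √4.5 = 2.1 at 50% initiation, and √2.31 = 1.5 to √2.60 = 1.6 at 75%. As an example, planning uses a standard error of 4.0 × √(2/80) = 0.63 visits. At an assumed mean of 3, the Poisson test would use √(2 × 3/80) = 0.27.

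**8. Alternatives under the null.** With means of 2-4, SD 4.0-4.5 and negative binomial counts, a quasi-Poisson F test rejected 5.2-6.0% of the time and a robust-variance log rate ratio 5.3-6.6%. With 50% zeros built in, the robust test gave 5.1-6.6%. A plain negative binomial likelihood ratio test there ranged from 0.2% to 7.9%, and was below 1% at means of 3 or more.

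**The case against.** **The SD is borrowed.** It comes from three studies of adolescents who had attempted suicide or were already recognised as suicidal, whereas this trial excludes suicidal and psychiatric presentations. Their follow-up windows, and whether their SDs include non-attenders, cannot be seen from the protocol. This stands as a limit on the size of the problem. It does not remove it. If the SD described attenders only (mean μ among them, half attending), phi would be (0.5 × SD² + 0.25 × μ²)/(0.5 × μ), which is never below 2 × √(0.5 × SD²) = 5.7 to 6.4, so that reading makes matters worse. A much milder pattern, with mean 1.5 and SD 1.8, gives phi = 3.24/1.5 = 2.16 and still about 18%.

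**The plan leaves room to notice.** Variables to be Measured allows transformation or non-parametric methods for skewed data, and provides for regression diagnostics with residual plots. These could bring overdispersion to light. But they name neither dispersion nor a remedy, the diagnostics are aimed at collinearity and influence, and the Poisson test is fixed specifically for this outcome. An SAP that is not shown might add a correction; the protocol as written does not.

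**Stronger readings.** A reader might infer a definite false-positive rate, such as one in two. The documents do not support that, because they give no mean. A reader might also count every false positive as a false claim for STAT-ED; only about half would be. Finally, a reader might infer that the trial's main comparison is compromised. It is not: initiation, the primary outcome on which the sample size rests, is compared by chi-square, and its 66 per group reproduces for 50% versus 75% with continuity correction.

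**Conclusion.** The concern holds for the number of sessions attended. The Poisson assumption and test contradict the protocol's own SD and initiation rate for that outcome. With the SD applied to all randomised participants and 50% initiation in both arms under the null, the two-sided type I error is at least about 33-36%. If initiation were 75% in both arms, the lower bound would be about 20-22%. The upper end depends on the unstated mean: about 33-54% for assumed means of 2-4 visits. The bound depends on the borrowed SD being about right for this population; a smaller SD would reduce the excess.

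Because this test is fixed in the protocol and serves part of a primary hypothesis, it should be changed before the data are analysed.

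**What to change.** In Variables to be Measured, both in the general paragraph and under Hypothesis 1, remove the Poisson distributional assumption and replace the Poisson likelihood ratio test and model-based Poisson standard errors with one of these:

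- a log-linear mean model (Poisson estimating equations) with robust sandwich standard errors, or
- quasi-Poisson with dispersion estimated from the data and an F test.

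Include arm and site as terms, report the rate ratio with its 95% CI, and use the same variance in the adjusted and interaction models. Name one method as the primary one. Do not substitute a plain negative binomial likelihood ratio test: with this share of zeros it is badly miscalibrated, almost never rejecting at means of 3 or more.

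The cost is a few sentences of wording and wider confidence intervals. No extra patients or data are needed. The existing detectable-difference calculation already rests on an SD, so it fits the corrected analysis better than it fits the Poisson test.

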### **Sample Size Justification**

Power analyses. All power calculations are for 2-sided tests,  $\alpha=0.05$ , and require power of 80%.

The primary outcome of mental health treatment initiation used in the sample size calculation is the proportion of participants who have attended at least one mental health visit in the 2 months after the ED visit, as assessed by the independent evaluator and verified with the mental health provider. Using a  $\chi^2$  test of proportion with continuity correction, power estimates for detecting differences in rate of treatment initiation during follow-up in the intervention and control group were computed using an expected rate of treatment initiation of 50% in the EUC arm. Under this assumption, the study will require 66 patients per treatment group to detect an intervention effect of 50% improvement in mental health treatment initiation (Table 4). We increased the number of participants to 80 per group to account for possible attrition and the chance of a lower rate of treatment initiation in the EUC group. With regard to the number of overall outpatient treatment sessions attended during follow-up, with 80 participants in each group, we are able to detect a difference in mean number of visits of between 1.7 and 2.2 (98). These calculations were based on an expected standard deviation  $\approx$  4.0-4.5 visits obtained from data reported by Spirito (34), Rotheram-Borus (33), and Asarnow (35).

On the basis of prior work, we anticipate retaining over 85% of participants for repeated assessment. For the primary aim, we will use an intent-to-treat analysis (ITT), and hence retain all 160 subjects. We will monitor the reasons for withdrawal, and use sensitivity analysis with missing data methods to assess the effects of withdrawal.

### **CONFIDENTIALITY/SECURITY**

Research records will be stored in a locked cabinet or file room in a secure location at all times. Research records will be stored in a password-protected computer file with limited access. The list linking the assigned code number to the individual subject will be maintained separately from the other research data and other PHI. Only certified research personnel will be given access to identifiable subject information.

### **PROCESS FOR OBTAINING INFORMED CONSENT AND ASSENT**

Recruitment procedures are designed with the goal of recruiting a clinically representative sample under real-world practice conditions. Consequently, the study recruitment method involves the identification of eligible youth through NCH and CCHMC emergency departments. Eligible patients and their parents/guardians will be approached to see if they are interested in learning more about the study. If they are interested, staff will describe the study and ask about possible study participation. For families interested in study participation, staff will ask the parent to grant consent in writing for youth to participate in the study and youth will be asked to grant their assent in writing. Consent and assent forms will contain: (1) the names, titles, addresses, and phone numbers of the investigators; (2) a description of the project; (3) a description of payment, risks, and benefits; (4) a statement of confidentiality; (5) a statement that acceptance or refusal to participate will not influence their ability to receive care; and (6) that they are free to withdraw their participation at any time. Subjects will be informed that, if abuse is disclosed during the study interviews, the appropriate authorities will be informed, for the protection of the child and in accordance with State and Federal laws. Subjects and parents will

also be informed if adolescents provide information regarding significant risk of harm to self or others, licensed social workers will talk with the family to determine what steps might be needed to provide the best clinical care and maintain safety. The child and parents will understand their rights under HIPAA and the Study Certificate of Confidentiality.

#### **LOCAL FACILITIES/PERFORMANCE SITES**

This research will take place at two sites, CCHMC and NCH. Participants will be recruited and enrolled in the Emergency Department of both locations. The data will be stored and analyzed at CCHMC.

#### **FUNDING PLAN**

Study funds to support this project will be provided through an R01 grant mechanism awarded by the Center for Disease Control and Prevention. Please see grant in appendix.

#### **COMPENSATION**

Participants will be compensated for their time and effort \$20 at baseline and \$20 after completion of the two and six month follow-up calls. Thus each family will receive sixty dollars total, with the parent getting \$30 and the adolescents getting \$30 for all procedures.

#### **DATA SAFETY AND MONITORING PLAN**

The principal investigators (PIs) will bear final responsibility for the oversight of subject safety monitoring during this study. In addition, a Data Safety Monitoring Board (DSMB) has been compiled to commensurate the risk associated with the intervention used in this clinical trial. The DSMB will be chaired by a researcher not currently involved with the study, [name]., Ph.D. Professor of Psychiatry, The Ohio State University College of Medicine and Nationwide Children's Hospital. [name], an experienced psychiatrist and researcher, conducts research on interventions for bipolar disorders in children. He will convene the DSMB, which will be comprised of at least one additional child mental health services or intervention researcher and a local practicing mental health clinician to inform the clinical perspective. The DSMB will serve as an independent data safety monitor to provide the oversight and monitoring necessary to ensure the safety of study participants and the validity and integrity of the data.

The DSMB will meet two times per year, will prepare annual reports to relevant regulatory agencies that summarize study recruitment and data quality, and will communicate with the relevant agencies and individuals should study findings suggest a shift in the study's risk to benefit ratio. They will work with the study's data administrator to perform interim data analyses with the assistance of statisticians not directly involved in the study. The DSMB will make recommendations based on these findings to the PIs, the IRB, and other regulatory agencies as appropriate, particularly with regard to whether continued study enrollment is both ethical and safe. The initial review will take place when 20 subjects have been enrolled.

